# 9.0 STATISTICAL CONSIDERATIONS

## 9.1 General Design Issues

This is a prospective, single-arm, 72-week pilot study to estimate the first-phase viral decay constant (d1) in treatment-naïve subjects initiating a three-drug regimen consisting of the HIV-1 integrase inhibitor RAL and NRTI combination FTC/TDF.

In general, analyses that address mechanisms of pathobiology will be conducted on subjects as treated (AT), and analyses of markers for clinical outcome will be ITT. The accrual target of 34 subjects is expected to yield plasma HIV-1 RNA data from 30 subjects for model-fitting, and thus provide a 95% CI around the estimated d1 of no wider than ±0.07, assuming the population mean and standard deviation of d1 for the study regimen are 0.80 and 0.20, respectively. Under these assumptions, with usable data from 30 subjects, there is 98% probability that the CI around the estimated d1 will exclude the value 0.65.

Subjects who modify the study regimen or miss doses are expected to stay on study and be followed; however, they will be replaced as follows: If the subject changes the regimen or misses any dose from day 0 through 14, an additional subject will be accrued. For every three subjects who change regimen or miss 2 or more doses from day 15 through 56, an additional subject will be accrued. (Although subjects dropping out before day 57 will be replaced in this way, the buffer of 4 additional subjects [Section 9.4] is retained to allow for missing results on obtained samples.) Such subjects will be excluded from AT analyses and included in ITT analyses. (See Section 9.6 for details.) From day 57 and thereafter, subjects altering the treatment regimen or missing doses will not be replaced; those who alter the regimen or miss more than 7 cumulative days of doses will be excluded from AT and included in ITT analyses.

The primary objective will be analyzed when plasma HIV-1 RNA results through day 28 are available (as quantified using the standard assay). Specifically, when the last subject to enroll has reached day 21, sites will be asked to send those batched plasma HIV-1 RNA samples that are intended for standard assay to the assay lab (Johns Hopkins University). When results for these samples and when the real-time results for the day 28 and 56 samples are available, analysis to estimate first and second phase viral decay rates will begin.

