## 9.4 Sample Size and Accrual

A total of 34 subjects will be accrued. Assuming subject enrollment from at least 7 sites, and a rate of 2 subjects every 3 months at each site, accrual is expected to be completed within 7.5 months.

The primary objective of the study is to estimate the first-phase viral decay rate in treatment-naïve subjects receiving RAL and FTC/TDF. As was done in ACTG viral dynamics substudies A5160s (parent study A5142) and A5166s (parent study A5095), plasma HIV-1 RNA levels will be measured at pre-entry and entry (geometric mean of these to be used as baseline) and as per the Schedule of Events. Plasma HIV-1 RNA measurements through day 56 will be used in estimating the first and second phase viral decay constants d1 and d2. Measurements obtained after treatment interruptions and/or rebound will be excluded. A parametric nonlinear mixed effects model for bi-exponential decay will be fit to the remaining on-treatment data, yielding subject-specific empirical Bayes estimates (EBEs) of d1 and d2. Ninety-five percent CIs around the subject-specific estimates will be reported.

Estimates of d1 obtained for subjects on ACTG A5166s and A5160 are shown in Table 6. For both studies, the difference in d1 between the arms with the best and poorest outcomes (highest and lowest d1; also lowest and highest rates of virologic failure in the parent study) was 0.11. For the three treatment groups in A5166s, population mean estimates (± standard deviations), derived from the estimated covariance matrix on the parameter estimates arising from the Markov chain Monte Carlo (MCMC) approach, ranged from 0.58±0.06/day to 0.70±0.18/day. An alternate derivation, from the 25th and 75th percentiles around the EBEs reported in Table 2 of the manuscript, and using the rule of thumb that the interquartile range is approximately equal to 1.35 times the standard deviation,(43) yields somewhat smaller estimates of 0.10 and 0.12, respectively.[[1]](#footnote-2) When the same back-calculations are applied to the EBEs for d1 reported in the final analysis report for A5160s, standard deviations (SDs) of d1 are estimated as 0.09, 0.18 and 0.09 for arms A, B and C, respectively. Móltó et al. reported d1 estimates of 0.80 and 0.62 for their 5- and 4-drug regimens, respectively (a difference of 0.18 between arms); SDs around these estimates were given as 0.13 and 0.18, respectively.(44)

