## 9.6 Analyses

9.6.1 Primary Objective

Primary objective: To estimate the first-phase viral decay rate in treatment-naïve subjects receiving RAL and FTC/TDF.

The primary analysis will be an AT analysis. Plasma HIV-1 RNA levels collected on days 0 to 56 will be used in parameter estimation except for (1) those collected after discontinuation, interruption, dose modification, or non-adherence to either RAL or FTC/TDF during days 0-14 (as determined from treatment records and adherence questionnaires), and (2) those at or after the first sign of rebound (defined as a rise of >0.30 log10 above the previous plasma HIV-1 RNA level). (For a given subject, HIV-1 RNA levels collected prior to such an event will be included in the analysis.)

Population and subject-specific decay parameters d1 and d2 from the bi-exponential model will be estimated by fitting a parametric nonlinear mixed-effects model to log10 plasma HIV-1 RNA levels.(4;5;10;45) Model-based 95% CIs around population estimates for d1 and d2 will be reported, and the distribution of subject-specific estimates will be summarized.

For any plasma specimen for which the HIV-1 RNA level is below the lower limit of detection (LLD) of the Ultrasensitive Roche Amplicor HIV-1 Monitor assay (50 copies/mL), a separate stored sample will be assayed for HIV-1 quantification using the single copy assay. In the event that any such single copy assay results are below the single copy assay LLD (1 copy/mL), to achieve unbiased estimates of d1 and d2 in the presence of censoring imposed by the assay lower LLD, an iterative multiple imputation procedure will be used.(5;45) This procedure is described in detail in the analysis plan.

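### Sections 9.1, 9.4 and 9.6.1 give incompatible data rules for the primary as-treated d1/d2 analysis, and 9.6.1 can leave off-treatment values in the fit

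*Protocol*

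**What the plan says.** Section 9.6.1 fixes the population for the primary objective: "The primary analysis will be an AT analysis". Three places then say which data enter it.

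- **Section 9.1, by subject.** Two triggers apply up to day 56: "If the subject changes the regimen or misses any dose from day 0 through 14, an additional subject will be accrued", and "For every three subjects who change regimen or miss 2 or more doses from day 15 through 56, an additional subject will be accrued". The consequence is: "Such subjects will be excluded from AT analyses and included in ITT analyses". From day 57 the text adds: "those who alter the regimen or miss more than 7 cumulative days of doses will be excluded from AT and included in ITT analyses". The day 0-56 exclusion carries a pointer to Section 9.6 for details.
- **Section 9.4, by measurement, with no day limit.** "Measurements obtained after treatment interruptions and/or rebound will be excluded". The model is fitted to what remains, described as on-treatment data.
- **Section 9.6.1, by measurement, with a day limit.** Day 0-56 values are used except "those collected after discontinuation, interruption, dose modification, or non-adherence to either RAL or FTC/TDF during days 0-14", and except those at or after a rise of more than 0.30 log10 over the previous value. The subject is kept: "For a given subject, HIV-1 RNA levels collected prior to such an event will be included in the analysis".

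**The concern.** The three rules act on different units (subject or measurement) and on different windows (days 0-14, days 0-56, or beyond). Two analysts following different sections would fit different datasets to the primary endpoint. Under 9.6.1 alone, a viral load drawn after an interruption on days 15-56 stays in the fit unless it rises enough to count as rebound, which does not match an as-treated label.

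The subject-specific d1 values are part of the primary endpoint (9.2.1). They also feed the signed rank test against 0.67 (9.6.2.1) and the associations with CD4+ restoration and activation (9.6.2.11 and 9.6.2.12). In an open-label, single-arm study, leaving the dataset open allows the choice to be made after the data are seen.

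**Working it through.** **1. The rules side by side.** Take a subject who misses three doses around day 18 and has no rise above 0.30 log10.

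| Section | Result for this subject |
|---|---|
| 9.1 | Whole subject removed (2 or more missed doses on days 15-56) |
| 9.4 | Values to day 14 kept; days 21, 28 and 56 dropped |
| 9.6.1 | All values kept |

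**2. The plan's own figures.** Inputs from 9.1 and 9.4: mean d1 0.80, SD 0.20, n = 30, reference value 0.65. Half-width = t(0.975, n-1) × SD/√n = 2.045 × 0.20/√30 = 0.0747 (0.0716 with 1.96), shown as 0.07. The probability that the interval lies above 0.65, from the noncentral t with noncentrality 0.15/(0.20/√30), is 0.978, against the stated 98%. Both reproduce.

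**3. Effect on one subject's fit.** The documents give no d2 or intercept ratio, so these are assumptions: d1 = 0.80, d2 = 0.04, first- to second-phase intercept ratio P1/P2 = 150, no noise. Model: log10 V(t) = log10[P1·exp(-d1·t) + P2·exp(-d2·t)] at days 0, 2, 7, 10, 14, 21, 28 and 56. The listed visits are raised by 0.2, 0.3 or 0.4 log10 and the curve is refitted by least squares.

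| Visits raised | Fitted d1 (+0.2 / +0.3 / +0.4) | Fitted d2 (+0.2 / +0.3 / +0.4) |
|---|---|---|
| 21 and 28 | 0.853 / 0.877 / 0.898 | 0.041 / 0.042 / 0.042 |
| 21 only | 0.833 / 0.848 / 0.864 | 0.042 / 0.043 / 0.044 |
| 21, 28 and 56 | 0.828 / 0.841 / 0.854 | 0.031 / 0.026 / 0.021 |
| 28 and 56 | 0.797 / 0.795 / 0.793 | 0.029 / 0.023 / 0.018 |
| 56 only | 0.776 / 0.764 / 0.753 | 0.029 / 0.024 / 0.018 |

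The largest visit-to-visit rise in any of these is 0.28 log10, so the rebound rule removes none of them. Varying the ratio from 50 to 300 and d2 from 0.03 to 0.06, one at a time, widens the d1 range to about 0.72-0.90. At d2 = 0.03, the rebound rule catches a 0.4 lift that begins at day 21 or 28 (rise 0.31).

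**4. Effect on the mean.** Section 9.4 quotes about 14% excluded for interruptions in A5166s: 0.14 × 34 = 4.8, say 5. If all five had the most extreme upward pattern, the shift would be 5 × 0.098/34 = 0.014. With the mildest pattern on days 21 and 28 it would be 5 × 0.053/34 = 0.008. With the most extreme day-56-only pattern it would be 5 × 0.047/34 = 0.007 downward. These fits are unshrunken; a mixed-effects fit would pull extreme subjects towards the mean.

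A small illustrative simulation points the same way. It used 34 subjects, d1 0.80 (SD 0.20), d2 0.05, assay SD 0.2 log10, 15-30% interrupted on days 15-56, and six replicates only. Sections 9.4 and 9.6.1 differed by about 0.002-0.003 in mean d1, and d2 was about 3-8% lower under 9.6.1. Sections 9.1 and 9.6.1 differed by about 0.01-0.03, but that run did not apply the 9.1 replacement rule and so dropped too many subjects.

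**5. Number analysable under 9.1.** Day 0-14 cases are replaced one for one, and k day 15-56 cases by floor(k/3). Five early cases leave 34 - 5 + 5 = 34. Five late cases leave 34 - 5 + 1 = 30. At SD 0.20 the half-width is 0.070 at n = 34 and 0.075 at n = 30; the probability of excluding 0.65 is 0.989 and 0.978.

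**The case against.** The strongest reply is that the document supplies a hierarchy. The 9.1 account of the analysis sets opens as a general statement and points to 9.6, 9.4 is a sample-size summary, and 9.6.1 is the specific rule. Section 9.6.2.1 also defines its as-treated data by reference to 9.6.1. This shows which text was probably meant to govern, but it does not remove the conflict. Section 9.6.1 reverses the subject-level exclusion instead of detailing it, and 9.4 still disagrees with 9.6.1 on days 15-56. Attaching the day 0-14 limit to non-adherence alone, a less natural reading, would bring 9.6.1 close to 9.4 but leave 9.1 in conflict.

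The reply is right about size. Three stronger readings are tempting and are not supported:

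- **That retained values bias d1 upward.** The sign depends on which visits are affected. Raising day 56 alone lowers d1, and raising days 28 and 56 leaves it almost unchanged.
- **That five affected subjects leave 29 for analysis.** The replacement rule in 9.1 leaves 30 to 34 when the events fall on days 0-56, and 30 is the planned number.
- **That doses missed months later would alter the d1 dataset.** This follows only if 9.1 is read literally over 9.6.1, which has no such trigger. Section 9.1 also starts the decay-rate analysis once day 56 results are in, and the day-57 clause has a natural use in later as-treated analyses such as third-phase decay.

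**Conclusion.** The contradiction is on the page and concerns the primary endpoint. As written, the primary dataset is not determined, and the 9.6.1 rule admits off-treatment values from days 15-56 into an as-treated fit.

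The numerical consequence for mean d1 is small: about 0.01 with five of 34 subjects affected, and 0.014 if all five share the worst pattern, against a half-width of 0.07. The 14% behind the five counts all A5166s interruption exclusions, so fewer may fall on days 15-56. Individual d1 values (about 0.75-0.90 against 0.80) and d2 values (about 0.018-0.044 against 0.04) can be distorted more. Those ranges rest on the assumed decay parameters and the assumed 0.2-0.4 log10 lift. The planned precision and the 98% probability are not materially threatened. The case for correction is that the dataset should be fixed in advance and match its as-treated label.

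**What to change.** State one measurement-level rule in 9.6.1 and align 9.1 and 9.4 to it:

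- Each subject contributes all values from day 0 up to the first regimen change or interruption on days 0-56, or up to the first rebound, and none after.
- An interruption is defined by the thresholds already in 9.1: any missed dose on days 0-14, and 2 or more missed doses on days 15-56. A single missed dose on days 15-56 would not censor.
- For the d1/d2 analysis, the whole-subject rule in 9.1 governs accrual replacement only.
- Events after day 56 do not affect the d1/d2 analysis.

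The cost is wording in three sections and the loss of a few post-interruption day 21-56 values that would otherwise inform d2. No new data are needed, because 6.3.5 already has interruptions recorded separately for entry to day 14, days 15-56 and later.

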5.1.2 Administration

Raltegravir

Raltegravir 400 mg tablets will be administered as one 400 mg tablet PO BID (800 mg per day), with or without food.

Emtricitabine/tenofovir disoproxil fumarate

Emtricitabine/ tenofovir disoproxil fumarate fixed-dose tablet containing 200 mg of emtricitabine and 300 mg of tenofovir disoproxil fumarate will be administered PO as one tablet QD, with or without food.

- - 1. Duration

Subjects will take their study medication for 72 weeks.

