6.3.5 ARV Treatment Modifications

During the study, all modifications to ARV drugs including subject-initiated and/or protocol-mandated interruptions and permanent discontinuation of treatment will be recorded on the CRFs at each visit. Subject-initiated and protocol-mandated interruptions of study medications include both inadvertent and deliberate interruptions of 1 dose(s), from entry to day 14, 2 doses from days 15 to 56, and >7 cumulative days thereafter.

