9.2.2 Secondary Endpoints

9.2.2.1 Population- and subject-specific first-phase plasma HIV-1 RNA level decay rates d1 (as estimated from biexponential decay models fit to plasma HIV-1 RNA level data through day 56).

9.2.2.2 Population- and subject-specific second-phase viral load decay rates d2 (as estimated from biexponential decay models fit to viral load data through day 56); population- and subject-specific third-phase decay rates d3 as estimated from plasma HIV-1 RNA levels obtained during weeks 24 to 72.

9.2.2.3 Proportion of subjects with viral load <50 copies/mL 24, 48, and 72 weeks after initiation of RAL and FTC/TDF. If the first detectable viral load corresponds to the sample collected at the last visit, the subject will be counted as detectable (at this visit) without confirmation.

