9.6.2 Secondary Objectives

9.6.2.1 To compare first-phase viral decay rates for RAL and FTC/TDF to first-phase viral decay rates estimated for the superior arms of A5160s and A5166s.

Primary analysis: The Wilcoxon signed rank test will be used to compare subject-specific d1 estimates (obtained as above) to the value 0.67, which was the point estimate from d1 obtained on the (EFV-based) superior arm of ACTG viral dynamics substudy A5166s.

Secondary analyses:

1. In an AT analysis (i.e., restricting the data as described in 9.6.1), plasma HIV-1 RNA levels from A5248 will be combined with data from A5166s and A5160s.(10;45;46) The resulting subject-specific EBEs of d1 will be compared using the permutation-based Kruskal-Wallis test. (In a 2001 simulation study, compared to parametric tests, Ding and Wu conclude that permutation-based tests outperform likelihood-based tests [maintain type I error rate, and are robust to deviations from normality and small amounts of missing data].(9) In the majority of published viral-dynamics applications, the nonparametric Wilcoxon test is used for inference to compare d1’s among 2 groups.)
2. This nonparametric comparison of subject-specific EBEs will be repeated, with additional plasma HIV-1 RNA levels from A5248 subjects: plasma HIV-1 RNA levels obtained after discontinuation or modification of FTC/TDF, and/or after no more than 7 cumulative days of prescribed RAL doses are missed.

9.6.2.2 To estimate the second- and third-phase viral decay rates in treatment-naive subjects receiving RAL and FTC/TDF, and to estimate the times at which subjects' decay rates transition from first to second phase and from second to third phase.

Subject-specific second-phase decay rates will be estimated along with first-phase decay rates as described in 9.6.1 above. Similar estimation and inference procedures will be used to estimate third-phase decay rates, based on single copy assay results for plasma HIV-1 RNA samples obtained during weeks 24 to 72.(20;21) The primary analysis will be AT; a secondary analysis may be conducted wherein subjects who discontinued or interrupted the regimen are retained.

Times of transition from first to second phase and from second to third phase will be estimated using the methods of Bosch and colleagues(47) applied to subject-specific predicted log10 HIV-1 RNA from days 0-56 (first to second phase) and applied to log10 HIV-1 RNA.

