9.6.2.3 To determine the proportion of subjects with plasma HIV-1 RNA below the limit of detection, <50 copies/mL, 24, 48, and 72 weeks after initiation of RAL and FTC/TDF.

The primary analysis will be an ITT analysis, wherein (1) if the study regimen (RAL and/or FTC/TDF) is modified or discontinued, the subject is retained in analyses, and (2) if a subject is lost to follow-up, the last observation is carried forward for subsequent time points. The proportion of subjects with plasma HIV-1 RNA <50 copies/mL at weeks 24, 48, and 72 will be reported along with the exact binomial 95% CI.

A secondary AT analysis will include only those subjects on the study regimen at the time of the evaluation.

9.6.2.4 To evaluate the safety and tolerability of the treatment with RAL and FTC/TDF.

Among subjects taking one or more doses of study drug, the proportion exhibiting each category of events will be reported, along with exact binomial 95% CI. Incidence rates, i.e., numbers of events per person-months of follow-up, will also be reported.

9.6.2.5 To evaluate changes in CD4+ T-cell counts 24, 48, and 72 weeks after initiation of RAL and FTC/TDF.

For the primary analysis, using the ITT approach described in 9.6.2.3, changes in CD4+ T-cell counts at weeks 24, 48, and 72 will be summarized descriptively via mean, SD, median, and quartiles. A secondary AT analysis may also be performed.

9.6.2.6 To investigate the occurrence of RAL and FTC/TDF-resistance mutations at virologic failure using very sensitive resistance assay techniques

Among subjects who took any dose of study drug, for each failing subject, the list of resistance mutations present at failure, if any, will be displayed. Of failing subjects, the proportion with specific mutations (ones occurring frequently among A5248 failures, ones known to be associated with RAL resistance) will be reported along with exact binomial 95% CIs.

9.6.2.7 To evaluate the relationship of RAL and FTC/TDF PK parameters with virologic and immunologic responses, including day 7 plasma HIV-1 RNA change from baseline and the magnitude and slope of changes in CD4+ T-cell counts over the first 14 days of study drug.

RAL, TDF, and FTC PK trough averages at steady state will be estimated.

9.6.2.8 To evaluate adherence by self-report in treatment-naïve subjects receiving RAL and FTC/TDF.

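### Section 9.1 drops whole subjects from as-treated analyses after 7 cumulative missed days, while 9.6.1 and 9.6.2.12 drop only later samples; the rule for third-phase and late DNA decay is not fixed

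*Protocol*

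**What the plan says.** **The exclusion rule.** Section 9.1 covers the period after the first eight weeks: "From day 57 and thereafter, subjects altering the treatment regimen or missing doses will not be replaced". It continues that "those who alter the regimen or miss more than 7 cumulative days of doses will be excluded from AT and included in ITT analyses". What is excluded is the subject. Section 6.3.5 uses the same threshold, ">7 cumulative days thereafter", to define an interruption that must be recorded.

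**The late analyses that depend on it.** Section 9.2.2 defines "third-phase decay rates d3 as estimated from plasma HIV-1 RNA levels obtained during weeks 24 to 72". For this analysis Section 9.6.2.2 states: "The primary analysis will be AT; a secondary analysis may be conducted wherein subjects who discontinued or interrupted the regimen are retained". Section 9.6.2.9 makes the analysis of proviral DNA, with samples through week 72, as-treated and descriptive. It offers no analysis that retains interrupters.

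**AT elsewhere in Section 9.6.**
- 9.6.1, for d1 and d2, drops samples after the event and adds: "For a given subject, HIV-1 RNA levels collected prior to such an event will be included in the analysis".
- 9.6.2.12 excludes endpoints from samples taken after an interruption or modification.
- 9.6.2.3 goes by status at the visit: "A secondary AT analysis will include only those subjects on the study regimen at the time of the evaluation".

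**The concern.** The protocol uses one label, AT, for three different rules and does not say which governs the long-term decay analyses. The choice decides which data are analysed.

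Under the literal 9.1 rule, a subject who passes the cap in week 70 is removed. With that subject go the single-copy results from weeks 24, 36, 48 and 60 and the DNA results from weeks 12, 24 and 48, all collected before the cap was crossed. Under the 9.6.1 or 9.6.2.12 rule they stay. The literal rule therefore wastes samples in a 34-subject study. It also makes inclusion of a week-24 value depend on what the subject did a year later. Section 2.1 describes defining the second and third phases as a critical secondary objective, so the analysis set deserves one clear definition.

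**Working it through.** **The plan's own figures.** The protocol states no percentage for the cap and no precision for d3 or DNA decay. The precision it does state is for d1, and it reproduces. With n = 30 and SD 0.20, the half-width is 1.96 × 0.20/√30 = 0.072 (0.075 with the t quantile), against the stated ±0.07. With mean 0.80 and reference 0.65, the probability that the interval lies above 0.65 is 97.8% (noncentral t), against the stated 98%. These rest on data through day 56, so the late cap does not touch them.

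**What the cap allows.** Section 5.1 sets the duration: "Subjects will take their study medication for 72 weeks", which is 72 × 7 = 504 days. From day 57 that leaves 504 − 56 = 448 days. Then 7/448 = 1.56%, so a subject followed to week 72 must take at least 98.4% of doses to stay in AT. The cap is a fixed count, so the floor depends on follow-up:

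| Followed to week | Days from day 57 | Minimum adherence, 1 − 7/days |
|---|---|---|
| 24 | 112 | 93.8% |
| 36 | 196 | 96.4% |
| 48 | 280 | 97.5% |
| 60 | 364 | 98.1% |
| 72 | 448 | 98.4% |

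For comparison, Section 8.2 takes a subject off study for missed doses only above 25% since the last visit. Over a 12-week interval that is 0.25 × 84 = 21 days. A subject can be well past the AT cap and still be on study and sampled.

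**How many subjects would remain (assumed adherence).** The protocol gives no adherence distribution, so this is a range. Count 7 days as 14 of the 896 twice-daily raltegravir doses (448 × 2).

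- *Same adherence in everyone, misses independent.* P(Binomial(896, 1 − p) ≤ 14) is 96%, 21%, 0.4% and about 0% for p = 99%, 98%, 97% and 95%. Counting whole days instead, P(Binomial(448, 1 − p) ≤ 7) is 92%, 33%, 4% and about 0%.
- *Adherence varying between subjects (beta-binomial).* The share still under the cap at each visit is:

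| Mean (SD) adherence | Week 24 | Week 48 | Week 72 | Of 34 at week 72 |
|---|---|---|---|---|
| 0.98 (0.02) | 95% | 72% | 56% | 19 |
| 0.97 (0.03) | 87% | 58% | 43% | 14 |
| 0.95 (0.05) | 72% | 42% | 29% | 10 |

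Under whole-subject exclusion the week-72 share applies to every visit. Under truncation at the event each visit keeps its own share. For the middle row, truncation raises the usable share at week 24 from 43% to 87% and at week 48 from 43% to 58%. It adds nothing at week 72.

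**The case against.** **Whole-subject deletion is not settled.** Section 9.1 introduces its AT/ITT split as a general approach, and its parallel rule for the first 56 days points to 9.6 for details. Section 9.6.2.2 says that third-phase estimation will follow procedures similar to those of 9.6.1, where earlier samples are kept. This stands. A reader might infer that the protocol commits to deleting every such subject, but the documents are inconsistent rather than decided. On the other side, the wording in 9.6.2.2 about retaining interrupters in a secondary analysis suggests that the primary one removes them as subjects.

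**Less adherent subjects are not absent from every late analysis.** A reader might infer that late decay would be seen only in near-perfect takers. Section 9.6.2.2 permits an analysis with interrupters, and 9.6.2.10 reports an ITT proportion below the single-copy limit for weeks 24 to 72. This also stands, with limits: the first is optional, the second is not a decay rate, and neither covers DNA.

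**Removing viremia caused by missed doses is the purpose of AT.** Section 9.1 assigns mechanism questions to AT, and suppression below 50 copies/mL is already ITT in 9.6.2.3. A reader might infer that the late decay estimates would be too favourable. The documents do not show this, and no direction or size of bias in a decay rate has been derived. The purpose of AT does not, however, require discarding samples taken before any lapse.

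**The stakes are modest, and the loss figures rest on assumptions.** This is a pilot. The single-copy decay rate will be estimated only if enough values exceed the assay limit, and the DNA analysis is descriptive. The protocol does not define a day of doses for a regimen with one twice-daily and one once-daily drug, and retention swings widely with assumed adherence. This is accepted; the figures show a possible size, not a forecast.

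**Conclusion.** The point holds as an internal conflict with a practical consequence. Section 9.1 excludes subjects, 9.6.1 and 9.6.2.12 exclude later samples, and 9.6.2.3 uses status at the visit; nothing settles which applies to d3 and late DNA decay. Followed literally, 9.1 loses valid on-treatment samples and conditions inclusion on later adherence. The cap of 1.6% of days is firm arithmetic for a subject followed to week 72 and looser for shorter follow-up. The estimate of about 10 to 19 of 34 subjects remaining depends on assumed mean adherence of 95% to 98% with the between-subject SDs shown. At a uniform 99% adherence nearly all subjects would remain. The change is worth making because it recovers data already planned for collection.

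**What to change.** Reconcile the passages. State in 9.1, 9.6.2.2 and 9.6.2.9 that values collected up to the time a subject alters the regimen or exceeds 7 cumulative missed days are included in AT, and that later values are excluded. Replace the optional analysis retaining interrupters with a fixed sensitivity analysis, for both d3 and DNA decay.

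The cost is wording only: self-reported adherence and treatment modifications are already collected at each visit after entry. There are two downsides. Subjects will contribute unequal numbers of visits, and a mixed model deals with that only if the truncation is ignorable. The latest visits will also still come only from subjects under the cap, so truncation does not remove the selection there. The fixed sensitivity analysis is needed to show its effect.
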